### Monitoring and harms

An independent monitor, the Clinical Research Bureau (CRB) of the VU University Medical Center, will monitor the data of this study according to GCP. The CRB will check the following aspects of the participants: (1) informed consents, (2) source data verification, (3) the reported (serious) adverse events ((S)AEs). Considering the nature of this study, SAEs are not expected. All AEs that are reported spontaneously by the participant or observed by the research staff or therapists will be recorded. All SAEs will be reported by the investigator to the sponsor, and the sponsor will inform the accredited Medical Ethics Committee (MEC).

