## Methods-design

### Design

The REMIND-MS study is a dual-centre, single-blind RCT with three parallel groups: CRT, MBCT and ETAU. All interventions last nine weeks in total. Measurements take place at baseline, post-intervention and after a 6-month follow-up period. The full trial design is summarised in Fig. 1.

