### Interventions

All interventions last nine weeks. The CRT consists of nine 2.5-h group sessions, MBCT of eight 2.5-h group sessions and one ‘silent day’, and enhanced treatment as usual (ETAU) of one individual appointment within the 9-week period. For CRT and MBCT, the optimal group size was determined based on previous experiences. Groups will consist of a maximum of 6 people in the CRT group and a maximum of 10 people in the MBCT group. Professionally trained psychologists will guide the CRT sessions, certified mindfulness trainers will teach the MBCT sessions and MS specialist nurses will have appointments with participants from the ETAU group. All trainers will be instructed and supervised by the same specialists. The interventions will be provided in a standardised manner using a written protocol. The trainers are instructed not to disclose treatment information to trainers from another treatment arm. All participants will receive an information brochure on MS and cognition.

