#### Adherence

For all groups, attendance to the sessions will be documented. For the CRT group, adherence to homework assignments will be checked and evaluated during each visit of the treatment period. For the MBCT group, adherence will be assessed during the entire treatment period with a calendar on which participants fill out whether they adhere to both formal (e.g. the sitting meditation) and informal (e.g. 3-min breathing space) mindfulness exercises.

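### Adverse events are recorded only if volunteered or observed, and CRT and MBCT have nine staffed contacts in nine weeks against one in ETAU, so any by-arm tabulation is liable to differential ascertainment

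*Protocol article*

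**What the plan says.** Under Monitoring and harms, the article states how adverse events come to be recorded: "All AEs that are reported spontaneously by the participant or observed by the research staff or therapists will be recorded". It adds that serious events are not expected, that an independent monitor checks the reported events, and that serious events go to the sponsor and the ethics committee.

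Under Interventions, contact with staff differs by arm. "The CRT consists of nine 2.5-h group sessions"; the mindfulness arm consists of "MBCT of eight 2.5-h group sessions and one ‘silent day" in addition; and ETAU consists "of one individual appointment within the 9-week period". Under Adherence, the CRT arm has a further routine occasion for talking about how things are going: "adherence to homework assignments will be checked and evaluated during each visit of the treatment period".

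The assessments are common to all arms (Design): "Measurements take place at baseline, post-intervention and after a 6-month follow-up period". Randomisation follows the baseline assessment. Under Randomisation and blinding, assessors are blind to allocation; participants and therapists are not.

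**The concern.** Passive recording depends on having someone to tell, or someone who notices. A CRT or MBCT participant meets a trainer about weekly during treatment, whereas an ETAU participant meets the specialist nurse once. The same headache, fall or low mood has more chances of reaching the record in the active arms, and the people who would note it there know which treatment is being given.

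Two errors of interpretation become possible if events are later shown by arm. An excess in CRT or MBCT could be read as harm when it is only closer observation. Conversely, a real excess could be dismissed as an artefact of observation. The article describes this as the first randomised trial of MBCT on cognitive function in MS, so readers may well look to it for information on harms.

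**Working it through.** The article gives no adverse event rate or power for harms, so there is no planned figure to reproduce. The check is a count of contacts, followed by an illustration under stated assumptions.

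**Scheduled contacts after randomisation**

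| | CRT | MBCT | ETAU |
|---|---|---|---|
| Intervention contacts in nine weeks (Interventions) | 9 | 8 + 1 = 9 | 1 |
| Shared assessments: post-intervention, 6 months (Design) | 2 | 2 | 2 |
| Total | 11 | 11 | 3 |

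The ratio of active arm to ETAU is 9/1 = 9 within the treatment period and 11/3 = 3.7 over the whole period after randomisation. CRT against MBCT is 11/11 = 1. The MBCT silent day is counted as a staffed contact.

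**Illustration of what this could do to recorded risk**

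Assumptions, none from the article: the true risk R is equal in all arms; each contact captures an existing event with the same probability q, independently; and the event is open to capture at all k contacts. Then

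recorded risk = R × (1 − (1 − q)^k)

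R cancels from the ratio, which is (1 − (1 − q)^11) / (1 − (1 − q)^3) over the whole period.

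| q | 9 vs 1 contacts | 11 vs 3 contacts |
|---|---|---|
| 0.02 | 8.3 | 3.4 |
| 0.1 | 6.1 | 2.5 |
| 0.2 | 4.3 | 1.9 |
| 0.5 | 2.0 | 1.1 |

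For example, at q = 0.1 with 11 vs 3 contacts: (1 − 0.9^11) / (1 − 0.9^3) = 0.686 / 0.271 = 2.5.

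With 40 per arm, R assumed at 0.2 to 0.4 and q from 0.02 to 0.5, a two-sided 5% comparison of recorded proportions on 11 vs 3 contacts would be significant with probability between about 5% and 47%, although the true risks are equal.

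Two features limit these figures. The ratio approaches the contact ratio only when capture per contact is very unlikely; as q rises, capture saturates and the ratio falls towards 1. And an event that first arises after the post-intervention assessment meets one scheduled contact, the 6-month assessment, in every arm, so its expected ratio under this model is 1.

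**After the fix**

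If the same question is asked only at the two shared assessments, k = 2 in every arm and the expected ratio is 1.0 for any q common to the arms.

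**The case against.** The strongest reply is that nothing planned is biased. Safety is neither an objective nor a listed outcome, and the section on primary and secondary objectives confines the between-arm models to the outcome measures. A reader might infer from the rule that the trial's harms comparison is biased. The article states no such comparison, so this stands against that reading; what remains is a caution about any tabulation by arm.

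A reader might also infer that harm in ETAU, or harm after the sessions end, would go largely unseen. The article does not support this. Research staff are a named source of reports and see all arms at both later assessments. Anxiety and depression, fatigue and rumination are measured equally in every arm, as are medication use and health care consumption. After the sessions, scheduled contact is the same in all arms. These measures are not designated as sources of adverse events, however, so they soften the problem without removing it.

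The size can fairly be disputed too. Equal capture per contact is doubtful: a group session of up to 6 or 10 people is not the same as an individual nurse appointment, and participants may report events between contacts. Against that, participants are reminded before each post-measurement not to reveal their group, which may discourage mention of an event tied to meditation or group work at exactly the visits that are shared.

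Finally, passive recording is an openly stated choice in a behavioural trial, and the article condenses a fuller protocol whose case report form is not shown. But the recording rule is itself stated here, so the point concerns a method that is fixed, not a detail left out.

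**Conclusion.** The point holds as a minor one. Followed as written, the rule makes detection of adverse events liable to differ between each active arm and ETAU, most probably with more events recorded in CRT and MBCT at equal true risk. The firm quantities are the contact counts: 9, 9 and 1 during treatment, and 11, 11 and 3 in all.

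The size of any distortion cannot be derived from the article. The ratios of 1.1 to 3.4 over the whole period show only what equal true risk and an assumed capture probability of 0.02 to 0.5 would imply. It would be too strong to say that recorded events will differ by 9 to 1, that the active arms are bound to look worse, or that counts cannot be compared at all: each needs a capture probability that the document does not give.

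The comparison of CRT with MBCT is balanced on number of contacts. The analysis of the CFQ and the other efficacy analyses are unaffected.

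**What to change.** At the existing post-intervention and 6-month assessments, give every participant in all three arms the same self-completed adverse event question. Base any by-arm summary of harms on these solicited answers. Continue to record spontaneous and staff- or therapist-observed events as now, but list them separately and mark their source. The reporting of serious events does not change.

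The cost is one form item at two existing time points and a field in the electronic case report form. Self-completion fits the questionnaires that participants can already fill in at home, and helps keep the assessor blind provided that the answers are not shown to the assessor. The drawbacks are recall over about six months at the last assessment, and a few more minor events to record. The recall period is the same in every arm, so it lowers sensitivity without restoring the imbalance in contacts.

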## Discussion

The best treatment options for cognitive problems in MS patients are still a matter of debate. This study will therefore investigate the effect of two promising non-pharmacological treatments: MBCT and CRT. To our knowledge, this will be the first RCT that investigates the effect of MBCT on cognitive function among MS patients. In addition, studying the effect of CRT on cognitive function may provide direction to the contradictory evidence that is currently available [12, 13]. If these treatments appear to be effective, we will investigate which factors predict this beneficial effect. These prognostic factors may lead towards tailored treatments for MS patients who suffer from cognitive problems.

An important strength of our study is that we use functional brain network measures, such as functional connectivity and nodal centrality, as an outcome variable. These measures may help to explain treatment effects and may provide information on whether network deterioration can be halted. Additionally, if functional brain network measures at baseline predict treatment outcomes, network analyses can be used as a prognostic factor. We will also relate functional brain network measures to objective and subjective cognitive problems in MS, which may help to understand the overlap and distinctiveness between these types of cognitive problems.

In summary, this study may help to unravel and treat cognitive problems among MS patients.

## Abbreviations

AE: Adverse event
BRIEF-A: Behaviour Rating Inventory of Executive Function – Adult Version
BVMT-R: Brief visuospatial memory test-revised
CFQ: Cognitive failure questionnaire
CIRS: Cumulative illness rating scale
CIS-20-r: Checklist individual strength-20-r
COWAT: Controlled oral word association test
CRB: Clinical Research Bureau
CRT: Cognitive rehabilitation therapy
CVLT: California verbal learning test
CWO: Scientific Research Committee
D-KEFS: Delis-Kaplan Executive Function System sorting test
EDSS: Expanded disability status scale
ETAU: Enhanced treatment as usual
FFMQ-SF: Five facets of mindfulness questionnaire short form
GAS: Goal attainment scale
GCP: Good clinical practice
HADS: Hospital anxiety and depression scale
JLO: Judgment of line orientation test
KR: Klimmendaal Rehabilitation Center
MBCT: Mindfulness-based cognitive therapy
MEC: Medical Ethics Committee
MEG: Magnetoencephalography
MHC-SF: Mental Health Continuum-Short Form
MS: Multiple sclerosis
MSNQ-P: Multiple Sclerosis Neuropsychological Questionnaire – Patient version
MSQoL-54: Multiple sclerosis quality of life questionnaire
MST: Minimum spanning tree
RCT: Randomised controlled trial
REMIND-MS: Cognitive Rehabilitation and Mindfulness in Multiple Sclerosis
RRS-NL: Dutch Ruminative Response Scale
SAE: Serious adverse event
SCS-SF: Short form of the self-compassion scale
SDMT: Symbol digit modalities test
TIC-P: Questionnaire on healthcare utilisation and productivity losses in patients with a psychiatric disorder
USER-P: Utrecht Scale for Evaluation of Rehabilitation – Participation
VUmc: VU University Medical Center
